#### Covariate Adjustment and Confounder Control

Following the framework established by Chinman [32], the models will control for critical pharmacological and clinical confounders. To account for the different intervention durations between waves, intervention exposure duration will be included as a time-varying covariate. Antipsychotic treatments will be categorized into high-risk (eg, clozapine and olanzapine) and low-to-moderate risk groups, also incorporated as time-varying covariates to account for any regimen changes during the 6-month period. To isolate the intervention’s effect from “pseudo-weight loss” caused by medication nonadherence, medication possession ratios will be calculated; participants with a medication possession ratio <80% will be analyzed as a separate subgroup in sensitivity analyses. Additionally, stratified analyses based on baseline weight status (overweight vs obese) will be conducted to explore potential moderating effects.

Missing data will be addressed via multiple imputation under missing at random assumptions. Further sensitivity analyses, including pattern mixture models and tipping point analysis, will be performed to evaluate the impact of potential missing not at random mechanisms. To mitigate the risk of type I error inflation across multiple secondary and subgroup analyses, the false discovery rate correction will be applied. All analyses will be conducted using SAS 9.4, with clinical and feasibility implications prioritized over nominal statistical significance.

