## Methods

### Study Design

This study uses a pragmatic, open-cohort SW-CRT with a 2-month step duration. The trial spans a total observation window of 6 months across 6 clinical units at a tertiary hospital in Beijing. The SW-CRT design ensures that all participants eventually receive the intervention, fulfilling ethical requirements for this high-risk population, while the staggered rollout allows the implementation team to maintain high fidelity by providing intensive technical training for 1 wave at a time.

The trial addresses the dynamic turnover of psychiatric hospitalizations (average stay 4‐6 wk) by defining each cluster as a clinical unit rather than a fixed physical location. The research team comprises trained research assistants, certified nutritionists, and sports physicians. Participants are typically enrolled during their stable recovery phase in the ward; however, the intervention is designed to be portable. Following discharge, the intervention continues remotely, with the same clinical team providing longitudinal oversight via digital clinician dashboards. This approach enables the evaluation of the intervention across the transition from inpatient care to community-based recovery.

The 6 units were randomized into 2 waves (3 units per wave) using a matched-pair constrained randomization approach. To ensure baseline balance, units were paired based on clinical setting and demographics. Allocation was managed by an independent biostatistician via REDCap (Research Electronic Data Capture; Vanderbilt University) and remained concealed from the recruitment staff and participants.

The study timeline is structured into three distinct phases:

Baseline phase (month 1): all clusters receive usual care to establish stable baseline metrics.Transition phase (2 weeks): a staggered 2-week period for device distribution and technical training, occurring at month 1 for wave 1 and month 3 for wave 2.Intervention phase: active digital monitoring lasting 5 months for wave 1 (months 2-6) and 3 months for wave 2 (months 4-6).

This open-cohort approach accounts for the dynamic turnover of psychiatric hospitalizations, allowing for individual enrollment while maintaining randomization at the cluster level (Figure 2).

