### Patient Recruitment

Due to the dynamic turnover of psychiatric hospitalizations, an open-cohort approach was adopted, allowing for continuous recruitment throughout the study period. Recruitment follows a structured clinician-referral model across the 6 clinical units to ensure both clinical appropriateness and implementation fidelity. The process is organized into the following stages: Treating psychiatrists identify potential participants during routine clinical encounters in the outpatient and inpatient departments. Patients are considered for referral if they meet three prerequisites: (1) a BMI ≥24 kg/m², (2) a demonstrated interest in weight management, and (3) a confirmed stable clinical phase, defined as a minimum of 4 weeks on a stable medication regimen.

Upon referral, an independent project physician conducts a formal in-person screening session. This involves a review of the patient’s electronic health records (EHR) to confirm *ICD-10* (*International Statistical Classification of Diseases, Tenth Revision*) diagnoses and physical measurements of height, weight, and blood pressure. To ensure the validity of historical data, the exclusion criterion regarding significant prior weight loss is ascertained through a multi-informant approach, cross-referencing patient interviews with collateral reporting from family caregivers and EHR data. Detailed inclusion and exclusion criteria are summarized in Textbox 1.

Textbox 1.Inclusion and exclusion criteria.

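### A subgroup defined by a medication possession ratio measured largely after crossover cannot isolate the intervention's effect from weight loss due to nonadherence

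*Protocol article*

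**What the plan says.** The section Covariate Adjustment and Confounder Control gives both the aim and the method. The aim: "To isolate the intervention’s effect from “pseudo-weight loss” caused by medication nonadherence, medication possession ratios will be calculated". The method: "participants with a medication possession ratio <80% will be analyzed as a separate subgroup in sensitivity analyses". The article prints no window for the ratio, no data source and no counting rule.

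The same section treats the antipsychotic risk category as time-varying. The possession ratio, by contrast, is used to classify participants.

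On timing, Study Design states: "The trial spans a total observation window of 6 months across 6 clinical units". Month 1 is usual care for all units. The intervention phase is months 2-6 in wave 1 and months 4-6 in wave 2. Statistical Plans, Overview sets intention to treat for all analyses.

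**The concern.** The aim is causal: to tell weight lost through the programme from weight lost because drug was not taken. The method sorts participants by something observed while the programme is running. If the programme changes drug supply, membership of the low-ratio group depends partly on response to the programme, and a comparison within that group is no longer between groups that randomisation made alike.

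A single label also carries no timing. The pattern that matters most is a fall in supply once the intervention starts. The label does not distinguish it from a fall during usual care.

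At stake is how this analysis will be read. A similar effect in both subgroups could be taken as proof that the weight result is not a medication artefact, and a different effect as proof that it is. Neither conclusion would follow.

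**Working it through.** The article gives no sample size, power or error rate for this subgroup, so there is no printed figure to reproduce. The check has four steps.

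**1. When the ratio is measured.** The stated target is nonadherence that produces weight loss in the trial, so the ratio has to cover follow-up. This is an inference from the purpose. For a participant followed for all 6 months, the share of the window after crossover (timeline in Study Design) is:
- wave 1: 5/6 = 83%
- wave 2: 3/6 = 50%

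**2. What one label can show.** Let r_u and r_i be the ratios under usual care and under intervention. Assume one ratio over all 6 months, with the 2-week transition counted as usual care.
- Wave 1: R = (1·r_u + 5·r_i)/6. Wave 2: R = (3·r_u + 3·r_i)/6.
- With full supply under usual care (r_u = 100%), R reaches 80% at r_i = (480 − 100)/5 = 76% in wave 1 and at r_i = (480 − 300)/3 = 60% in wave 2. An intervention-period ratio between 60% and 76% therefore puts a wave 1 participant in the subgroup but not a wave 2 participant.
- With full supply under intervention (r_i = 100%), wave 1 cannot fall below (0 + 500)/6 = 83.3%, whatever happens in its usual-care month. Wave 2 reaches 80% at r_u = 60%.
- In wave 2, the pairs (r_u, r_i) = (100%, 60%) and (60%, 100%) both give exactly 80%. The label cannot tell them apart.

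**3. Whether the programme could move the ratio.** It brings clinician dashboards (Study Design), psychiatrist oversight and weekly messages (Intervention Program), counselor outreach and in-person support for nonadherence to the programme (Outcomes and Measures, Overview), and calls or clinic invitations after missed weigh-ins (Table 2). This contact could raise drug supply; attention to weight could also lower it. Table 1 lists no component aimed at medication adherence, so an effect is plausible but not established.

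**4. Size of the selection effect under assumptions.** Simulation with no true effect on the outcome and 2,000,000 participants per setting. A is intervention (0/1), U is a latent trait, and e and e′ are independent standard normal errors:
- ratio = 0.85 + 0.08·U + shift·A + 0.08·e
- outcome = g·U + √(1 − g²)·e′

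All parameters are assumed. Results are intervention minus control, in SD units:

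| shift | g | overall | ratio <80% | ratio ≥80% |
|---|---|---|---|---|
| 0 | 0.3 | −0.001 | −0.001 | −0.001 |
| 0 | 0.5 | −0.001 | 0.000 | −0.001 |
| 0.05 | 0.3 | 0.000 | −0.069 | −0.044 |
| 0.05 | 0.5 | 0.000 | −0.117 | −0.073 |
| 0.10 | 0.3 | 0.000 | −0.146 | −0.076 |
| 0.10 | 0.5 | −0.002 | −0.247 | −0.128 |

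The overall contrast stays at zero while both subgroup contrasts move away from it. The subgroup contrast is proportional to g, so its sign reverses if the trait relates to the outcome in the opposite direction.

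The simulation compares full exposure with none. In this trial a period-specific shift d moves the 6-month ratio by 5d/6 in wave 1 and 3d/6 in wave 2, a between-wave difference of d/3. The table therefore shows the mechanism and does not forecast the bias here.

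**The case against.** The strongest reply is that the point is conditional. No window is printed, no component targets medication, and with no effect of the programme on the ratio the selection bias is zero. The analysis is labelled a sensitivity analysis, the main analyses are by intention to treat, and the primary generalized estimating equations model does not use the ratio. The plan also has other relevant elements: a time-varying antipsychotic risk category, at least 4 weeks on a stable regimen before referral, and medication adherence as an exploratory predictor.

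Most of this stands, and it limits the severity. Three things remain. A ratio meant to detect nonadherence during weight loss has to be measured during follow-up. The timing problem in step 2 exists even if the programme leaves drug supply unchanged. And the other elements address regimen changes, stability at entry or prediction; none compares drug supply between usual care and intervention.

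A reader might also infer that the ratio misclassifies inpatients, because "Participants are typically enrolled during their stable recovery phase in the ward" and drug given on a ward is not dispensed to the patient. Over 180 days, a fully adherent participant would fall below 80% after more than 0.20 × 180 = 36 hospital days counted as unsupplied, and the average stay is 28 to 42 days. The documents do not support this reading. They give no counting rule for hospital days, excluding such days removes the distortion, and a definition of this kind is commonly left to the analysis plan. The 36 days must also fall within the study, whereas 4-6 weeks is the average total stay. Part of the stay may precede enrolment, and patients are also referred "during routine clinical encounters in the outpatient and inpatient departments". With 14 in-study days, even the least favourable rule gives (180 − 14)/180 = 92.2%.

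**Conclusion.** The concern holds in a limited form. As described, the low-ratio subgroup is defined by a variable that is, by inference from its purpose, measured largely after crossover. Contrasts within it are not protected by randomisation, and one label per participant cannot place a fall in supply under usual care or under the intervention. The claim to isolate the effect is stronger than the method allows.

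No size can be fixed from the documents. Under the assumed shifts of 0.05 to 0.10, the spurious contrast is 0.07 to 0.25 SD in absolute value below the cut and 0.04 to 0.13 SD above it, and it is zero without a shift. The conclusion rests on a follow-up window for the ratio and, for the selection part only, on some effect of the programme on drug supply.

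A reader might go further and infer that the primary result is compromised. It is not, because the primary analysis does not condition on the ratio. Severity is minor.

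**What to change.** Calculate the possession ratio separately for each participant's usual-care and intervention periods. Report it as an outcome by condition and wave, using the same time-adjusted model as the other outcomes, next to the weight effect. This shows directly whether drug supply falls under the intervention. Keep the <80% subgroup as descriptive only, and replace the word isolate with wording that claims no causal separation.

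Defining the subgroup by the ratio before crossover may look like a simple remedy, but it would miss nonadherence during the intervention, which is the event of interest. It would also often lack data: wave 1 has about one usual-care month, and participants enrolled after their unit's crossover have none.

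The cost is slightly more analysis work and a change of wording, with no change to trial conduct. The drawback is that period-specific ratios will be noisy or unavailable where usual-care time is short or absent, namely in wave 1 and for participants enrolled after crossover.

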### Sample Size Estimation

The sample size was powered based on the mean reduction in body weight (kg) to provide greater statistical sensitivity than binary outcomes. Drawing from meta-analyses of digital interventions for SMI [8] and the recent CoachToFit trial [32], a Cohen *d* of 0.40 was identified as a clinically realistic target effect size. Using PASS 2021 (stepped-wedge cluster-randomized design module) with 6 clusters and monthly repeated measurements, a total sample of 204 participants (34 per unit) provides 82% power (α=.05, 2-tailed) assuming a conservative intracluster correlation coefficient (ICC) of 0.10. This value is consistent with empirical benchmarks for metabolic outcomes in psychiatric institutional settings [43-45]. Furthermore, this sample size is sufficiently robust to detect the primary categorical outcome of ≥5% weight loss, assuming a 20% success rate in the control phase and a 40% success rate in the intervention phase (odds ratio≈2.6). Accounting for a 20% attrition rate (aligned with recent SMI trial observations), the final evaluable sample (n=163) maintains ≥75% power even under varying cluster performance, ensuring robust detection of the treatment effect under pragmatic constraints.

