### Statistical Plans

#### Overview

All analyses will follow the intention-to-treat principle. We prioritize effect size estimation over formal hypothesis testing. Implementation outcomes, including recruitment, retention, and adherence rates, will be reported with 95% CIs. For clinical intervention effects, we will report point estimates with 80% CIs to balance precision with exploratory use, as wider intervals better reflect the preliminary nature of these estimates and minimize the risk of overinterpreting early trends. To account for the different intervention durations between waves, intervention exposure duration (time since crossover) will be included as a time-varying covariate in the mixed-effects models. This approach allows for the estimation of the intervention effect while adjusting for the varying lengths of exposure across clusters.

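### Moderation by baseline weight status is to be explored through stratified analyses alone, which give two effects but no estimate or interval for their difference; an interaction term would supply it.

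*Protocol article*

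**What the plan says.** In Covariate Adjustment and Confounder Control, the protocol article states that "stratified analyses based on baseline weight status (overweight vs obese) will be conducted to explore potential moderating effects". The same section applies a false discovery rate correction across secondary and subgroup analyses.

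The linear mixed model in Clinical Effectiveness Analysis has a single intervention coefficient, categorical time terms, covariates, and random intercepts for unit and patient. The binary primary outcome is to be analysed by generalized estimating equations. No intervention-by-weight-status term, interaction test or between-stratum contrast is mentioned for either model.

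On reporting, the Overview of the Statistical Plans says "We prioritize effect size estimation over formal hypothesis testing" and, for clinical effects, "we will report point estimates with 80% CIs". The sample size section gives the overall power: the design "provides 82% power (α=.05, 2-tailed) assuming a conservative intracluster correlation coefficient (ICC) of 0.10", and after attrition "the final evaluable sample (n=163) maintains ≥75% power".

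**The concern.** The sentence names a method and a purpose, and the method does not deliver the purpose. To say that weight status moderates the effect is to say that two effects differ, so the quantity needed is their difference with its uncertainty. Two stratum estimates, each set against zero, do not provide it.

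What is at stake is how the results may be read. With only two stratum results on the page, it is easy to note that one interval excludes zero and the other does not, and to call that moderation. Each stratum has less information than the whole trial, so such a split is common even when the true effect is the same in both. Refitting the unit and time terms within each stratum, with six units, also spends information that a joint model can share.

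**Working it through.** **Inputs from the article.** Two-sided α 0.05; overall power 82%, or at least 75% after attrition; Cohen d 0.40; 204 patients in six units; 80% intervals for clinical effects.

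**Assumptions.** The article gives no overweight/obese split, so 50:50 to 70:30 is assumed. It gives no correlation between stratum estimates, so independence is taken first and then relaxed. There is no true moderation: the planned effect is the same in both strata.

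**The plan's own figure.** The 82% cannot be reproduced from the stated inputs, because cluster-period size and the within-person and between-period correlations are not given. Plausible stepped-wedge layouts ran from about 24% to nearly 100%. An individually randomised comparison of 102 with 102, ignoring clustering, gives 81.5%. The stated 82% and 75% are therefore taken as given. No power is stated for the subgroup analysis.

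**Step 1: overall signal.** λ = z(power) + 1.960.
- 82%: 0.915 + 1.960 = 2.875
- 75%: 0.674 + 1.960 = 2.634

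**Step 2: signal per stratum, independent strata.** A stratum with share f has λ√f. For f = 0.5 this is 2.033 (82%) or 1.863 (75%).

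**Step 3: chance that a stratum's 80% interval excludes zero.** p ≈ Φ(λ√f − 1.2816), plus a negligible lower tail. For f = 0.5, p = 0.774 or 0.720.

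**Step 4: chance that exactly one stratum excludes zero.** p₁(1 − p₂) + p₂(1 − p₁).

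| Overall power | Split | p₁, p₂ | Disagreement, 80% intervals |
|---|---|---|---|
| 82% | 50:50 | 0.774, 0.774 | 35.0% |
| 82% | 60:40 | 0.828, 0.705 | 36.5% |
| 82% | 70:30 | 0.870, 0.618 | 41.3% |
| 75% | 50:50 | 0.720, 0.720 | 40.3% |
| 75% | 60:40 | 0.777, 0.651 | 41.6% |
| 75% | 70:30 | 0.822, 0.567 | 45.7% |

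**Step 5: strata sharing the six units.** Shared unit effects make the two estimates positively correlated. With equal strata and correlation ρ, the overall variance is s²(1 + ρ)/2, where s² is the variance of one stratum estimate. The stratum signal is then λ√((1 + ρ)/2). Bivariate normal probabilities give, at the 80% level:

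| ρ (assumed) | 82% power | 75% power |
|---|---|---|
| 0.1 | 30% | 36% |
| 0.2 | 26% | 31% |
| 0.3 | 22% | 27% |
| 0.4 | 18% | 23% |

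Cluster-period calculations with a shared unit effect, with overall power fixed at 82%, gave 21% to 34%. Steps 4 and 5 together support roughly 20% to 45%.

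**Step 6: other comparison rules, independent equal strata.**
- Non-overlap of the two 80% intervals requires a difference of 2 × 1.2816 × s, against a standard error of √2 × s. That is z = 1.2816 × √2 = 1.812, a two-sided probability of 7.0%.
- With p-values at 0.05 and a Benjamini-Hochberg correction over the two strata, exactly one is significant in 39% (82% power) or 38% (75%). The correction addresses multiplicity, not the missing contrast.
- With no effect in either stratum, exactly one 80% interval excludes zero in 2 × 0.2 × 0.8 = 32% of trials.

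**Step 7: the direct test.** An interaction test keeps its nominal error: 5% at α 0.05, and 20% if judged by an 80% interval. With equal independent strata, the standard error of the difference is twice that of the overall effect. For an interaction as large as the overall effect, the signal is 2.875/2 = 1.438 and power at α 0.05 is Φ(1.438 − 1.960) ≈ 30%. At 75% overall power it is 26%. Positive correlation between strata would raise these.

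**The case against.** The strongest reply is that the article does not commit the error of comparing significance between strata. It says only that moderation will be explored, it puts estimation ahead of testing, and it places clinical and feasibility meaning above nominal significance. That stands. A reader might infer that the plan will often report a false difference, in about half of trials, since 95% intervals and equal independent strata give 49.8%. The document does not support that reading. It states no rule for comparing the strata, it plans 80% rather than 95% intervals for clinical effects, and strata in the same six units are unlikely to be independent.

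It can also be said that stratified analyses might be drawn from one model with an interaction, that a reader could approximate the difference from two intervals, and that such detail belongs in an analysis plan not shown here. This stands in part: separate fitting is the natural reading but is not spelled out. Yet the article does more than omit detail. It chooses a method for a moderation question, and the only model it writes out has one common intervention effect.

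Finally, the interaction estimate will be imprecise. That is true, and it is a reason to show the imprecision, not to leave the contrast out.

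**Conclusion.** The point holds as a minor one. As written, the plan yields an effect in each weight stratum but not the difference between them, which is the quantity of interest. How far this could mislead depends on a comparison rule that the article does not state. Disagreement would be roughly 20% to 45% if the strata are compared by which 80% interval excludes zero, and about 7% if compared by non-overlap of those intervals. The range rests on the stated 75% to 82% overall power taken at face value, no true moderation, an assumed split of 50:50 to 70:30, and assumed correlation between strata of zero to about 0.4. It is not a forecast that a false difference will be reported. The analysis is exploratory, and the primary outcome and main models are unaffected.

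**What to change.** Fit the models of Clinical Effectiveness Analysis to all patients, adding baseline weight status and its product with the intervention term. Report the interaction estimate with its interval, and derive the overweight and obese effects from that same fit. As a check, repeat with continuous baseline BMI in place of the two categories. Since a joint model assumes common time trends unless told otherwise, a second check can let the time terms differ by weight status. State that the strata will be compared through the interaction estimate and not by which interval excludes zero.

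The cost is one model term, its main effect and a sentence of text; no new data are needed. The price in interpretation is a wide interval, so the plan should say that an inconclusive interaction is not evidence of equal effects. The Results section reports that initial analysis is under way, so the change should be dated, with a note of whether any subgroup results had been seen.
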